##### Drop-out criteria

(1) the disease progressed to a great extent during the intervention (tumor recurrence or metastasis); and (2) Other forms of psychotherapy are received during the study.

Sample size will be estimated based on previous research with a medium to small effect size [44]. With a power of 0.90, an alpha set at 0.05, and an effect size of 0.47 for the primary outcome of FACT-G scores, each group will be 29 women [21]. We estimate a 30% attrition rate based on an attrition rate of 28.8% in previous research [45]. A minimum of 76 women (38 in each group) are required.

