#### Randomization and blinding

Using the Excel software, the participants will be randomly divided into an intervention group and a control group with a ratio of 1:1. The randomization result will be placed in an opaque sealed envelope. Throughout the study, the participants, evaluators who will collect the data, and the data analysts will be blinded from the grouping information.

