### Statistical analysis

All data were analyzed using the Statistical Package for Social Sciences 22.0(SPSS Inc., Chicago, IL, USA). Two researchers will carry out data analyses.Participants’ characteristics and outcome scores were summarized using means ± standard deviation (SD) or medians [interquartile ranges (IQR)] for continuous variables or frequencies (percentages) for categorical variables. Baseline characteristics and outcomes were compared using independent samples t-test or Mann–Whitney U test from continuous variables and chi-squared test for categorical variables between the intervention and control group. *p* values < 0.05 were considered statistically significant. All analyses will be conducted on an intention-to-treat basis.

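### The attrition allowance is too small: 38 women per group leaves about 26–27 at the planned 30% loss, not the 29 the plan says it needs

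*Protocol article*

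**What the plan says.** The calculation is in the protocol article, Methods/design, in the paragraph that follows the drop-out criteria. Its design inputs are "With a power of 0.90, an alpha set at 0.05" and "an effect size of 0.47 for the primary outcome of FACT-G scores", and from these it concludes that "each group will be 29 women". It then allows for loss to follow-up: "We estimate a 30% attrition rate based on an attrition rate of 28.8% in previous research". The result is "A minimum of 76 women (38 in each group) are required".

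The paragraph does not print the formula that takes 29 to 38, and it states neither the type of effect size nor whether the test is one- or two-sided. Under Randomization and blinding, women are "randomly divided into an intervention group and a control group with a ratio of 1:1". Under Statistical analysis, the article says that "All analyses will be conducted on an intention-to-treat basis". The total of 76 is repeated in the abstract, and the Intervention section divides 38 intervention women into three WeChat groups.

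**The concern.** Two ways of allowing for attrition are in common use, and only one does what is intended. Multiplying the required number by 1 + d adds d as a share of the number to be kept. Attrition, however, is a share of the number randomised, so the required number has to be divided by 1 − d. At small d the two nearly agree. At d = 0.30 they do not: 1.30 × 0.70 = 0.91, so multiplying leaves only 91% of the target.

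The step from 29 to 38 looks like the multiplication. If so, the total presented as a minimum does not meet the plan's own target at the plan's own attrition rate, and the stated power of 0.90 is not delivered even if everything upstream is accepted. The figure also sets the size of the trial and of the WeChat groups.

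**Working it through.** **Inputs**, all from the sample-size paragraph: 29 per group to be retained; planned attrition 30%; source attrition 28.8%; 38 per group (76 in total) to be randomised; power 0.90; alpha 0.05.

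**1. Reproducing the plan's figure.**
- n × (1 + d) = 29 × 1.30 = 37.7, rounded up to 38 per group, 76 in total. This matches.
- n/(1 − d) at 30% = 29/0.70 = 41.4, rounded up to 42 per group, 84 in total. This does not match.
- n/(1 − d) at 28.8% = 29/0.712 = 40.7, rounded up to 41 per group, 82 in total. This does not match.

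**2. What 38 per group delivers.**
- At 30% loss: 38 × 0.70 = 26.6 per group (76 × 0.70 = 53.2 in total).
- At 28.8% loss: 38 × 0.712 = 27.1 per group.
- Largest loss that still leaves 29: 1 − 29/38 = 23.7%.

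These three results use only the printed 29, 38, 30% and 28.8%. They hold whatever formula was used.

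**3. What the shortfall costs in power.** Take the plan at its word that 29 per group gives 90% power. By the normal approximation, the standardised signal at n per group is then (z_alpha + 1.282) × √(n/29), and power = Φ[(z_alpha + 1.282) × √(n/29) − z_alpha]. The effect size cancels, so its type does not matter here.

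Two-sided, z_alpha = 1.960:
- n = 26: 3.242 × 0.947 − 1.960 = 1.109, power 86.6%.
- n = 27: 3.242 × 0.965 − 1.960 = 1.168, power 87.9%.

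The t-test version gives nearly the same: 86.5% and 87.8%.

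One-sided, z_alpha = 1.645:
- n = 26: 2.926 × 0.947 − 1.645 = 1.126, power 87.0%.
- n = 27: 2.926 × 0.965 − 1.645 = 1.179, power 88.1%.

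So the loss is about 2–3 points on either reading of sidedness.

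**4. Does 29 itself follow from the inputs?** This matters only for how far the corrected total can be trusted. If 0.47 is assumed to be a standardised mean difference in a two-group comparison, 90% power needs 96 per group two-sided or 78 one-sided. If it is assumed to be Cohen's f (equivalent to a standardised difference of 0.94), the two-sided need is 24–25. Neither assumption gives 29.

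**The case against.** Several points can fairly be made for the plan.

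- **The multiplication is inferred.** That is true, since no formula is printed. No division by 1 − d gives 38 at either attrition rate, so the inference is strong. In any case the shortfall in step 2 does not depend on it.
- **76 is called a minimum, so more could be recruited.** The wording does not cap recruitment. But the abstract plans 76, the Intervention section plans 38, and a minimum that fails on its own inputs is still wrong as a minimum.
- **Analysis is by intention to treat, and women lost late may contribute earlier assessments.** This stands in part. The figure of 26–27 is the position once the full planned loss has occurred, most naturally at the last visit. It does not remove the problem, because the plan itself inflates for attrition in order to keep 29, and an intention-to-treat label does not supply missing questionnaires.
- **The effect is small.** This stands. No estimate is biased, and the cost is 2–3 women per group.

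A reader might infer two stronger things. The first is that this slip leaves the trial with power of only about 40%. With 0.47 assumed to be a two-sided standardised difference, the normal approximation does give 43.2% at 29 per group and 39.5–40.8% at 26–27 (one-sided, 55.8% and 52.0–53.3%). The document does not say that 0.47 is such a difference, and on that assumption the low level comes almost wholly from the 29, with the attrition step adding only about 2–4 points. The second is that 84 is the right size for the trial. The documents do not support that either: 84 inherits a 29 that could not be reproduced, and on the same two-sided assumption even 42 per group with no loss would have 57.7% power.

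**Conclusion.** The point holds as an arithmetic error of modest size. On the plan's own inputs, 38 per group falls short of the 29 to be retained by 2–3 women per group at the planned attrition. Measured at randomisation, the gap is 4 per group, or 8 in total. The plan reaches its target only if attrition is at most 23.7%, below both the 30% it assumes and the 28.8% it cites.

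The power cost of 2–3 points is conditional on 29 per group giving 90% power, and that condition is not verified. The failure of 29 to follow from 0.47, read as a two-sided standardised mean difference, is a separate and larger problem that should be judged on its own. The attrition step should be corrected, but taken alone it does not threaten the trial's conclusions.

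**What to change.** Replace the attrition step with n/(1 − 0.30) and print the formula. Then take one of two routes.

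- **Keep 76.** State that it yields about 26–27 evaluable women per group at 30% attrition, and give the power for that number, with the type of effect size and the sidedness of the test. This costs a few sentences and no extra patients.
- **Change the total.** First re-derive the evaluable number per group from stated inputs, then divide by 0.70. Only if that re-derivation returns 29 should 42 per group, 84 in total, be given as the requirement. That would mean eight more women within the three-month recruitment period, a revised total in the abstract, and a revised split of the intervention arm, now 38 women in three groups of 12 to 13.

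The corrected formula is needed on either route: any re-derived number multiplied by 1.30 would again leave only 91% of its target at 30% attrition.

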#### Recruitment

The participants will be recruited from the gynecology outpatient department. Posters and flyers about this study will be posted and distributed in the outpatient center. An information sheet about the study will be given to the patients who verbally expressed their intention of participation. In order to make sure that they have enough time to read the information sheet, discuss with family members, and make the final decision, one week will be given to the patients. If a patient agrees, the contents, procedures, and rules of the study will be explained to her, and she will be asked to sign an informed consent. At the same time, oncology experts of this study will review the participants' medical records to obtain information about disease diagnosis, pathology, past and current cancer treatment, and patients' treatment compliance. Subjects will be screened according to the inclusion criteria. The recruitment period is expected to last for 3 months. Data will be collected before randomization (baseline), immediately after intervention (test 1), 3 months after intervention (test 2) and 6 months after intervention (test 3). The trial will be conducted in accordance with the Declaration of Helsinki and will take place from Jun 1, 2022 to Dec 31, 2023.

#### Randomization and blinding

Using the Excel software, the participants will be randomly divided into an intervention group and a control group with a ratio of 1:1. The randomization result will be placed in an opaque sealed envelope. Throughout the study, the participants, evaluators who will collect the data, and the data analysts will be blinded from the grouping information.

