### Study design

#### Trial design

A single-blinded, randomized, controlled, parallel group pre-test, and repeated post-test design will be conducted to investigate the effect of WeChat-based Cognitive behavioral therapy for Chinese gynecological cancer survivors.

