### Intervention

Patients in the control group will receive routine outpatient follow-up, during the visits, they will be provided general health recommendation, brief medication and exercise guidance, and information related to mental health. In addition, telephone follow-up will be carried out once a month. The patients are allowed to ask questions related to the disease through WeChat or mobile phone, yet they cannot participate in the online educational intervention.

For the intervention group, patients will receive group CBT for 10 weeks, carried out by psychiatrists, psychological counselors, and oncology nurses who had received CBT training. The details of intervention are described in Table 1. For the purpose of better communication, 38 patients in the intervention group were divided into three WeChat groups (12–13 patients in each group). The same intervention scheme was used in the three groups. Group CBT professionals will be invited to evaluate and supervise the intervention process.

**Table 1 Tab1:** The details of intervention

	Intervention Group	Control Group
Service	WCBT + routine care	Routine care
Provider	Researchers	Doctors and nurses
Place	Web environment	Hospital outpatient
Form	WeChat platform	Face-to-face
Contents	Cognitive reconstruction; Cognitive behavioral therapy; Support expression	Regular follow-up
Duration and frequency	The total intervention time not less than 10 weeks	Follow up at least twice
Assessment	Baseline (pre-intervention) Test 1 (immediately after intervention) Test 2 (3 months after intervention) Test 3 (6 months after intervention)	Baseline (pre-intervention) Test 1 (immediately after intervention) Test 2 (3 months after intervention) Test 3 (6 months after intervention)

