### Data collection

The patients will be identifed by a unique study inclusion number and by the frst initial of their surname and of their given name. Baseline data will be collected face-to-face immediately after the patients signing the informed consent. Test 1 will be performed immediately after the intervention, test 2 and test 3 will be performed 3 months and 6 months after the intervention, respectively. The "questionnaire star" app on the WeChat platform will be used during test 1, test 2 and test 3 to send online electronic questionnaire to each participant. The questionnaires included HADS, FACT-G, MSAS-SF, mini-MAC, BFS, socio-demographics, and clinical data.

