### Validity and reliability

The feasibility of this study design is high, and the measurement tools have high effectiveness and reliability. The statistical analysis method is appropriate, which can effectively reduce error. In addition, because the evaluators and data analysts are blinded from the patient group, biases in the evaluation of intervention outcome can be effectively controlled.

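### Participants are said to be blinded although the two arms are plainly distinguishable, and blinding evaluators and analysts does not control bias in outcomes the women rate themselves

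*Protocol article*

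**What the plan says.** Randomization and blinding names three blinded parties: "Throughout the study, the participants, evaluators who will collect the data, and the data analysts will be blinded from the grouping information". Trial design carries a different label, "A single-blinded, randomized, controlled, parallel group pre-test, and repeated post-test design will be conducted", and the abstract's Methods paragraph also calls the trial single-blinded.

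The Intervention section describes what each arm experiences. On one side, "For the intervention group, patients will receive group CBT for 10 weeks", in three WeChat groups of 12–13 women, with educational material twice a week, homework handed to a researcher and group discussion every one to two weeks. On the other side are routine outpatient follow-up and a monthly telephone call. Controls may ask questions through WeChat or by phone, "yet they cannot participate in the online educational intervention". No sham or attention-control programme is described.

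Data collection says an app will be used at tests 1, 2 and 3 "to send online electronic questionnaire to each participant", and lists HADS, FACT-G, MSAS-SF, mini-MAC and BFS among its contents. Validity and reliability then concludes: "because the evaluators and data analysts are blinded from the patient group, biases in the evaluation of intervention outcome can be effectively controlled". The three listed limitations cover the small, tertiary-hospital sample, the restriction to gynecological cancer, and the restriction to women willing to use WeChat. None mentions blinding.

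**The concern.** Two statements are at issue. The first is that participants do not know their group, which the described interventions rule out. The second is that blinding evaluators and analysts controls bias in evaluating the outcome. That argument works when someone other than the patient makes the rating. Here the patient makes it.

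Women who know they are in a CBT programme may score their anxiety, depression and symptoms differently from women who know they are not, for reasons other than the therapy's effect: expectation of benefit, or a wish to answer in a way that pleases the team. Several features exist in one arm only and make this plausible: researchers deliver the intervention, homework goes to a researcher, and active discussants receive a gift. Such a reporting difference cannot be separated from a treatment effect using the data this trial collects. A reader who accepts the two statements would credit the primary results with a protection the design does not provide.

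**Working it through.** The protocol article gives no figure on this point to reproduce, so the check sets its sections side by side.

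**Step 1. Can participants be blinded to grouping?**
- Recruitment: the study's contents and procedures are explained to each woman before she signs consent.
- Intervention: one arm joins a WeChat therapy group for 10 weeks; the other is excluded from the online programme.
- No sham or attention control is described.

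A woman can tell her arm from what she receives. This is an inference, but a firm one. Reading the sentence as blinding to the hypothesis does not rescue it, because what it says is concealed is the grouping.

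**Step 2. Do the blinding descriptions agree?**

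| Place | Description |
|---|---|
| Abstract, Methods; Trial design | Single-blinded, party not named |
| Randomization and blinding | Participants, evaluators and data analysts |
| Validity and reliability | Evaluators and data analysts, given as the reason bias is controlled |

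The conflict is between the first and second rows: a single-blind label against three blinded parties. The third row does not contradict the second, since it does not say anyone is unblinded.

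**Step 3. Who rates the outcomes?**
- Primary: HADS, MSAS-SF (2 scales).
- Secondary: FACT-G, mini-MAC, BFS (3 scales).
- All 5 are in the online questionnaire sent to participants at 3 post-tests: 5 × 3 = 15 scale-by-time assessments, all rated by the woman herself. The hypothesis under Aims is likewise framed as what patients report.
- Baseline is collected before randomization, so it is unaffected.
- WeChat usage and clinical variables, under Other outcomes, are not symptom self-ratings and fall outside the point.

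**Step 4. Does the validity claim follow?** Bias from knowing one's group enters when the questionnaire is answered. Blinded evaluators and analysts act after that. They can limit bias in data handling and analysis, but cannot remove bias already in the answers.

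**Step 5. What could a reporting shift do?** This is an illustration only; the shift *b* is assumed and has no basis in the documents. Suppose there is no true effect, unblinded reporting moves scores by *b* SD in favour of one arm, the test is a two-sided z-test at 0.05, and observations are independent. Then

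rejection rate = Φ(b/SE − 1.96) + Φ(−b/SE − 1.96), with SE = √(2/n) per arm.

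Using n = 29 and n = 38, the two group sizes in the sample-size paragraph, SE = √(2/29) = 0.263 and √(2/38) = 0.229.

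| Assumed b (SD) | n = 29 | n = 38 |
|---|---|---|
| 0 | 0.050 | 0.050 |
| 0.1 | 0.067 | 0.072 |
| 0.2 | 0.119 | 0.141 |
| 0.3 | 0.208 | 0.258 |

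For example, b = 0.2 and n = 29 give b/SE = 0.76, and Φ(−1.20) + Φ(−2.72) ≈ 0.119. At a fixed shift the rate is higher in the larger trial, so more women would not cure the problem. The table shows direction and mechanism; it does not estimate this trial's error rate.

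**The case against.** The best defence is that participants cannot be blinded in any comparison of group psychotherapy with routine care. The arms and questionnaires are described openly, and no sample size, test or estimate changes if the sentence is corrected. That is right as far as it goes: the design is not at fault for being open to participants. It does not excuse stating the opposite, or resting a validity claim on blinding that does not reach the rater.

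The defence also stands against several stronger readings a reader might infer:

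- *That the bias equals some share of the planned 0.47 effect.* The documents give no bias figure. The 0.47 belongs to FACT-G, which the sample-size paragraph calls primary but the outcome section lists as secondary, and its metric is not stated. Read as a standardized mean difference at two-sided 0.05 and 90% power, it would need 2 × (1.96 + 1.282)² / 0.47² ≈ 95.1, so 96 per group rather than 29. It is therefore not a safe denominator, and no planned effect is given for HADS or MSAS-SF.
- *That evaluators are not blinded, or do nothing but send a link.* The article says they collect data and are blinded. Nothing in it shows this is infeasible, and their full role at tests 1–3 is not described.
- *That analysts will be unblinded by WeChat usage data or group membership.* The article does not say analysts receive these before the primary analysis. How such files are held may be set out in the full protocol or analysis plan, so this is not a finding here.
- *That women know which arm is expected to do better.* Knowledge of allocation is clear. What they are told about the hypothesis cannot be seen.

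**Conclusion.** The point holds. The statement that participants are blinded to grouping is wrong for this design and does not fit the article's own single-blind label. The statement that evaluation bias is effectively controlled does not hold for HADS, MSAS-SF, FACT-G, mini-MAC or BFS at tests 1, 2 and 3, which means every primary and secondary scale at every post-randomization assessment.

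The amount of bias is unknown and cannot be identified from the planned data. The conclusion does not depend on the illustrative error rates. It rests on two readings of the text: that women can recognise their arm from the care they receive, and that an online questionnaire sent to a participant is completed by her. Blinding of evaluators and analysts is not disputed and remains worth having for data handling and analysis. The consequence is for interpretation: a between-group difference in anxiety, depression or symptoms would combine any therapy effect with any effect of knowing the allocation, and the article should say so.

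**What to change.** 1. In Randomization and blinding, remove participants from the list of blinded parties. State that participants and therapists are not blinded, and that evaluators and data analysts are. The section makes no claim about therapists at present, so naming them is a clarification.
2. Use that same description in the abstract, Trial design and Validity and reliability. If the single-blind label is kept, define it by naming the blinded parties.
3. Qualify the sentence in Validity and reliability: blinding evaluators and analysts limits bias in data handling and analysis, but not in self-rated outcomes. It need not be deleted.
4. Add unblinded self-report to Limitations, as a bound on what can be concluded about anxiety, depression and symptoms.
5. Do not attach a percentage of the 0.47 effect to the bias.

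The cost is wording only. Sample, interventions, instruments and tests are unchanged; the article gives up a more favourable description of its rigour.

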### Intervention

Patients in the control group will receive routine outpatient follow-up, during the visits, they will be provided general health recommendation, brief medication and exercise guidance, and information related to mental health. In addition, telephone follow-up will be carried out once a month. The patients are allowed to ask questions related to the disease through WeChat or mobile phone, yet they cannot participate in the online educational intervention.

For the intervention group, patients will receive group CBT for 10 weeks, carried out by psychiatrists, psychological counselors, and oncology nurses who had received CBT training. The details of intervention are described in Table 1. For the purpose of better communication, 38 patients in the intervention group were divided into three WeChat groups (12–13 patients in each group). The same intervention scheme was used in the three groups. Group CBT professionals will be invited to evaluate and supervise the intervention process.

**Table 1 Tab1:** The details of intervention

	Intervention Group	Control Group
Service	WCBT + routine care	Routine care
Provider	Researchers	Doctors and nurses
Place	Web environment	Hospital outpatient
Form	WeChat platform	Face-to-face
Contents	Cognitive reconstruction; Cognitive behavioral therapy; Support expression	Regular follow-up
Duration and frequency	The total intervention time not less than 10 weeks	Follow up at least twice
Assessment	Baseline (pre-intervention) Test 1 (immediately after intervention) Test 2 (3 months after intervention) Test 3 (6 months after intervention)	Baseline (pre-intervention) Test 1 (immediately after intervention) Test 2 (3 months after intervention) Test 3 (6 months after intervention)

The contents of CBT intervention is based on currently mature cognitive and behavioral treatment programs in the world [46–48], which includes psychological education and self-monitoring, cognitive reconstruction, behavior correction, relaxation training, and problem-solving technique. The contents can be divided into three components: (1) cognitive reconstruction: the purpose is to explain disease- and psychology-related knowledge for patients at different stages, such as the risk factors, common treatment methods, prognosis, common side effects and treatments, and common psychological problems of gynecological malignant tumors; (2) cognitive behavioral therapy, the purpose of which is to identify and change incorrect psychological cognition, and train the patient’s coping skills. It will be used through the treatment plan of this study. The core is to help patients correctly manage stress and improve self-confidence, identify and optimize the use of social support resources, etc.; (3) support expression. A topic will be selected for WeChat group discussion. Members share their experiences and emotional exchanges about the topic, and the members will be encouraged to talk about stress and negative emotions, so as to help members support each other and reduce loneliness. There will be 6 topics throughout the study: (a) start treatment with your medical team. Including self-introduction and mutual understanding; joint formulation of group norms; sharing of the illness experience and current troubles; expressing the feelings and hopes of participating in the group; (b) management of symptoms and side effects, such as fatigue, pain, and insomnia. In addition, how to identify physical tension and use relaxation techniques (meditation, muscle relaxation, etc.); (c) the role of emotion during rehabilitation. How to identify negative thoughts and share them; (d) body image and sex; (e) family and friends; and(f) self-management of a healthy lifestyle.

First, online education information, in the format of texts, pictures, sound and video will be shared twice a week through WeChat. Before or after the release of information, the patients will be reminded via WeChat notifications. The learning time per week should be no less than 1 h. All previous information will be available for the participants at any time throughout the study. Secondly, the participants are required to carefully study the educational content, and turn in homework to a researcher. Homework includes learning experience, self-reflection diary, self-portrait videos of various relaxation exercises, etc., the purpose of homework is to improve the self-learning and monitoring ability of the participants, and then the participants are expected to extend the methods to their daily life, thereby strengthening the effect of intervention. In addition, discussions in the WeChat group will be held every 1–2 weeks based on the educational content released weekly. A gift will be given to the participants who actively participate in the discussion. Throughout the intervention, the participants will be encouraged to raise questions and share their experiences at any time.

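### WeChat therapy groups make one arm clustered, but the only outcome tests named assume independence: if within-group ICC is positive, type I error exceeds 5%

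*Protocol article*

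**What the plan says.** Under *Randomization and blinding*, participants are allocated 1:1 as individuals, and participants, evaluators and data analysts are to be blinded to the allocation.

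Under *Intervention*, the treated arm receives ten weeks of group CBT, for which "38 patients in the intervention group were divided into three WeChat groups" of 12–13 women, all following one scheme. Interaction is a named treatment component: "the members will be encouraged to talk about stress and negative emotions, so as to help members support each other and reduce loneliness". Group discussions are held every one to two weeks. Controls receive routine outpatient follow-up and monthly telephone calls, with no group element.

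Under *Statistical analysis*, "Baseline characteristics and outcomes were compared using independent samples t-test" or the Mann–Whitney U test, with chi-squared for categorical variables, and p "values < 0.05 were considered statistically significant". No other between-arm method for outcomes is named.

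The sample-size paragraph, placed under *Drop-out criteria*, gives "With a power of 0.90", "an alpha set at 0.05" and "an effect size of 0.47 for the primary outcome of FACT-G scores". Neither it nor the analysis section mentions an ICC, a design effect or the WeChat groups.

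**The concern.** This is a partially nested design: women in one arm share a therapy group, and women in the other share nothing. If members of a WeChat group influence one another's anxiety, mood, symptoms or coping, which is part of how the treatment is meant to work, their outcomes are correlated. The mean of 38 treated women then carries less information than 38 independent observations. A t-test that ignores this understates the standard error of the arm difference, giving confidence intervals that are too narrow and too many false claims of a difference.

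The stake is whether a result near p = 0.05 can be attributed to the intervention or could reflect the character of three particular groups. If group membership is not recorded during delivery, it may be hard to recover later.

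**Working it through.** **The plan's own figure.** The plan states that "each group will be 29 women" before attrition, and 29 × 1.3 = 37.7, rounded up to 38, gives the stated total of 76. There is no clustering term in this. The 29 does not itself follow from the stated inputs by the usual two-sample formula: 2 × (1.960 + 1.282)² / 0.47² ≈ 95.2, so 96 per arm two-sided (78 one-sided). That is a separate matter. The check below uses 29 only as the number of completers the plan expects.

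**Inputs**
- 38 per arm, individually randomised 1:1 (*Drop-out criteria*; *Randomization and blinding*).
- Three groups of 12–13, taken as 13, 13 and 12 (*Intervention*).
- Controls unclustered (*Intervention*).
- Significance at 0.05 (*Statistical analysis*). Sidedness is not stated; two-sided is used here.
- ICC: not in the document. Values from 0 to 0.10 are assumed.
- Total variance taken as equal in the two arms.

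**Step 1: size-weighted group size.** m = (13² + 13² + 12²) / 38 = 482 / 38 = 12.68.

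**Step 2: design effect in the intervention arm.** DE = 1 + (m − 1) × ICC. At ICC 0.05: 1 + 11.68 × 0.05 = 1.584.

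**Step 3: true over naive standard error of the difference.** Only one arm is inflated, so the ratio is √((1 + DE) / 2). At ICC 0.05: √(2.584 / 2) = 1.137.

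**Step 4: actual type I error.** 2 × (1 − Φ(1.96 / ratio)). At ICC 0.05: 1.96 / 1.137 = 1.724, giving 8.5%.

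The formula was checked by simulating the ordinary t-test, 100,000 trials per ICC:

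| Assumed ICC | DE | SE ratio | Type I error, formula | Type I error, simulated |
|---|---|---|---|---|
| 0 | 1.000 | 1.000 | 5.0% | 5.1% |
| 0.01 | 1.117 | 1.029 | 5.7% | 5.6% |
| 0.02 | 1.234 | 1.057 | 6.4% | 6.3% |
| 0.05 | 1.584 | 1.137 | 8.5% | 8.3% |
| 0.10 | 2.168 | 1.259 | 11.9% | 12.0% |

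**With 29 completers per arm** (groups of 10, 10 and 9): m = (100 + 100 + 81) / 29 = 9.69. At ICC 0.05, DE = 1.434, the ratio is 1.103 and the simulated error is 7.5%. At ICC 0.10, DE = 1.869, the ratio is 1.198 and the simulated error is 10.4%.

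**Can three groups correct themselves?** A cluster-mean test with Satterthwaite degrees of freedom was simulated with 38 per arm. Its type I error was 6.1% at ICC 0.05 and 6.6% at 0.10. Its power for an effect of 0.47 was 34% and 29%. The uncorrected t-test rejects 52% and 53% of the time under that effect, but at the inflated error rates above, so the two are not like for like. A mixed model and the Mann–Whitney test were not simulated.

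**The case against.** Four points deserve weight.

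*The correlation is assumed.* A reader might infer that the standard errors are certainly wrong. The documents do not support that. Much of the treatment is individual: materials sent twice a week, at least an hour of private study, and homework handed to a researcher. All groups follow one scheme. A small ICC is plausible; at 0.01 the error is only about 5.6%, and at 0 there is no inflation. This stands, and the point must be conditional. A common scheme standardises content, however, not what happens between members of a particular group.

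*The t-test sentence may describe a baseline check.* A reader might infer that the plan commits to an independence-based test for the follow-up outcomes. The wording allows that reading but does not force it, and a full protocol or SAP that is not shown could add a group term. This also stands as a caveat. What remains is that no other between-arm test for outcomes is named.

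*A partially nested mixed model should become the primary analysis.* This is a tempting inference, but the article contains no mixed model to amend. With three groups, the cluster-mean test shown above gives up much power and still does not hold 5%. The objection stands against making such a model primary. It does not justify reporting only the result that assumes zero correlation.

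*Blinding.* A group variable filled in for one arm only reveals allocation to analysts who are meant to be blinded. This is correct and has to be handled in the fix.

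**Conclusion.** The point holds in conditional form. The stated layout creates therapy groups in one arm only, and the named tests ignore them. For any positive within-group ICC, the test is too liberal. Over assumed ICCs of 0.01 to 0.10, type I error is about 5.6% to 12% with all 38 per arm analysed, and about 7.5% and 10.4% at ICC 0.05 and 0.10 with 29 completers per arm.

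These figures rest on ICCs that the document does not supply, a two-sided t-test, equal total variance in the arms and near-equal group sizes. They do not show that the error rate is wrong in this trial; they show how far it could be off if the test is applied as written.

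**What to change.** 1. Under *Intervention*, state that intervention women are assigned to the three WeChat groups at random; the article says only that they were divided. If groups have already been formed, state how.
2. Record each woman's WeChat group as a trial variable.
3. Under *Statistical analysis*, state the between-arm test for outcomes at follow-up. Next to its estimate, report the confidence interval and p-value with the intervention-arm variance multiplied by 1 + (m − 1) × ICC at ICC 0, 0.01, 0.05 and 0.10, where m is the size-weighted group size among the women analysed. State whether the conclusion survives across that range.
4. A partially nested model (random intercept for WeChat group in the intervention arm only, small-sample degrees of freedom) may be added as a sensitivity analysis. It should not be required as primary, because three groups estimate the ICC poorly.
5. Release the group variable to the blinded analysts only after the main comparison is locked.

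Cost: one recorded variable, a few lines of analysis text and a staged data release. With 38 per arm, intervals are about 14% wider at ICC 0.05 and 26% wider at 0.10 (SE ratios 1.137 and 1.259), so a borderline result may not survive the upper end of the range.
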